### Study design

The intervention effects will be measured in a quasi-experimental controlled trial: the DISC (Diabetes in Social Context) Study. The participants who receive the intervention (PTWD, N = 128) will be compared with the participants of the comparison group (KYS, N = 128). In addition, the HbA1c levels of the participants in both groups will be compared with the HbA1c levels of 128 diabetic patients who will receive no intervention at all (standard care).

### Matching, blinding, recruitment, and informed consent

For the intervention to be successful, it is important that the participants live near each other. Therefore randomization is impossible. Therefore, the intervention and comparison group will be matched according to ethnicity, gender, and organization of diabetes care. Blinding the general practitioners (GPs) is impossible due to the nature of this study.

Recruiting people and maintaining participation in lower SE groups in intervention studies is difficult due to a low level of trust and insufficient understanding of the study and study procedures [35-38]. To increase trust and understanding, the eligible patients will be invited to a 'welcome meeting' about PTWD or KYS by their GP, a person they trust and respect. For people who do not speak Dutch, we will organize meetings in their mother tongue. At the welcome meetings, the eligible patients will receive detailed information about the study procedures. They will also take part in one of the intervention components (in PTWD groups, a short version of the game about nutrition, in KYS groups a short version of the diabetes quiz) to get an idea of what the intervention will be like. They will also meet their group leaders and the other patients and will see the intervention location, which we hope will lower barriers to participation.

At the end of the welcome meeting, the participants have two weeks to consider their participation. After two weeks they will be asked to sign an informed consent form in which they agree to participate in the intervention and give their consent for the study procedures. The informed consent form will be read to the diabetic patient and further explained if necessary. People who do not speak Dutch will receive the information in their mother tongue.

### Ethical considerations

This study has been approved by the Medical Ethics Committee of the Academic Medical Center (AMC) in Amsterdam, and is registered with the Dutch Trial Register (Dutch Trial Register NTR1886).

### Study population

We will include people with type 2 diabetes who received medical treatment long enough to achieve optimal glycaemic control (one year) but still have a HbA1c above 7% [39]. Inclusion criteria are at least one year since diagnosis, HbA1c > 7%, > 35 years, and living in a neighbourhood with low socioeconomic status. Exclusion criteria are GP objection to participation, severe psychiatric disorders, being unable to come to the intervention location independently, and planning to stay abroad for longer than six weeks during the intervention period.

Taking into account the prevalence of type 2 diabetes among ethnic minorities in lower SE groups in the Netherlands, we expect half of the study population to consist of ethnic Dutch patients and the other half to come from minority groups, in particular patients with Turkish, Moroccan, and Surinamese backgrounds.

### Sample size calculation

The primary outcome measure is the decrease in HbA1c at 16 months. A decrease of 0.5% in the intervention group compared to the comparison group will be seen as a difference that is clinically relevant. This means that at a statistical significance of 5% and a power of 80%, we will need 92 participants in both the intervention and the comparison group. Bearing in mind a dropout rate of 40%, we will need to include 128 people in both the intervention group and the comparison group.

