#### Blood and urine samples

In the Netherlands, HbA1c levels and fasting plasma glucose of diabetic patients are measured every three months. An extensive analysis of blood and urine samples is performed at least once a year [39]. For T0, T2, and T3, we will collect these data from the participants' medical records. More specifically, we will collect:

• Fasting plasma glucose, HbA1c, total cholesterol, high-density lipoprotein (HDL) cholesterol, triglycerides, creatinine, and creatinine clearance, glomerular filtration rate calculated according to the Modification of Diet in Renal Disease Study (MDRD equation)

• Microalbuminuria

In addition, we will use medical records to collect information on the participants' medication use and diabetes-related complications: retinopathy, cataract, kidney failure, microalbuminuria, myocardial infarction, angina pectoris, transient ischaemic attack (TIA), cerebrovascular accident (CVA), claudicatio intermittens, diabetic ulcers, amputation, polyneuropathy, and sensitivity problems in the feet.

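### At the plan's own 40% dropout, 128 per group leaves about 77 rather than the required 92, so 80% power holds only up to about 28% loss

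*Protocol article*

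**What the plan says.** The section on sample size calculation in the protocol article builds the number in three steps.

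- Outcome and target difference: "The primary outcome measure is the decrease in HbA1c at 16 months", and "A decrease of 0.5% in the intervention group compared to the comparison group will be seen as a difference that is clinically relevant".
- Requirement: "at a statistical significance of 5% and a power of 80%, we will need 92 participants in both the intervention and the comparison group".
- Allowance for loss: "Bearing in mind a dropout rate of 40%, we will need to include 128 people in both the intervention group and the comparison group".

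The section on study design carries the result forward: "The participants who receive the intervention (PTWD, N = 128) will be compared with the participants of the comparison group (KYS, N = 128". The abstract gives the same number. The article states no standard deviation, does not say whether the 5% is one- or two-sided, gives no inflation formula and does not define dropout.

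Two other places bear on what dropout would mean for the outcome. The section on blood and urine samples says "For T0, T2, and T3, we will collect these data from" the medical records, and HbA1c is among the items listed. The section on primary and secondary outcome measures names two primary outcomes at 16 months, HbA1c and diabetes-related quality of life. The second is measured by questionnaire in the structured interview (Table 2).

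**The concern.** A dropout rate is ordinarily a share of those enrolled. To finish with 92 after losing 40%, the requirement has to be divided by 0.60. The step from 92 to 128 is instead close to an increase of 40%, which is a smaller allowance. The sample size paragraph therefore assumes a loss that its own enrolment figure cannot absorb.

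At stake is the stated power of the main comparison, PTWD against KYS. If the assumed loss occurs and takes the outcome with it, the risk of missing a true 0.5% difference is higher than the 20% that a reader would take from the text.

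**Working it through.** **Inputs, all from the section on sample size calculation:** difference 0.5% HbA1c; significance level 5% (sidedness not stated, two-sided assumed here); power 80%; 92 per group required; dropout 40%; 128 per group enrolled. The standard deviation is not given.

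**1. Reproducing the plan's figure.** 92 × (1 + 0.40) = 128.8, which is 128 if truncated (129 if rounded up). This matches the printed number, but the article shows no formula, so it is a likely reconstruction only.

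**2. Inflation for a 40% loss.** Enrolled = required / (1 − dropout) = 92 / 0.60 = 153.3, so 154 per group. That is 154 − 128 = 26 more per group, or 308 instead of 256 over the two groups.

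**3. What 128 leaves.** 128 × (1 − 0.40) = 76.8, about 77 per group. Shortfall: 92 − 77 = 15.

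**4. Loss that 128 can absorb.** 1 − 92/128 = 0.281, about 28%.

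**5. Power with 77 per group.** No assumed SD is needed, because 92 per group at 80% power already fixes the ratio of difference to SD:

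- at 92 per group, difference / standard error = 1.960 + 0.842 = 2.802;
- at 77 per group, it becomes 2.802 × √(77/92) = 2.802 × 0.915 = 2.563;
- power = Φ(2.563 − 1.960) = Φ(0.603) = 0.727.

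The result is stable across reasonable choices: 72.1% with 76 per group, 72.6% with the noncentral t, and 73.6% if the 5% is one-sided. The type II error risk rises from 20% to about 27%.

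**6. Detectable difference.** With 77 per group and 80% power: 0.5 × √(92/77) = 0.547, about 0.55%.

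**7. The opposite extreme for HbA1c.** If a 16-month value were available for all 128 per group: 2.802 × √(128/92) = 3.305, and Φ(3.305 − 1.960) = 0.911. This is an upper bound that assumes no missing HbA1c.

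For reference, the SD implied by 92 per group is 0.5 / (2.802 × √(2/92)) = 1.21 two-sided (1.36 one-sided). None of these power figures allows for clustering of participants within meeting groups.

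**The case against.** The best counter-argument is that the 40% may not translate into lost HbA1c. The values come from medical records, the data collection section has those records studied at every measurement point, and mixed models can use partial follow-up. Someone who leaves the meetings may still have a 16-month HbA1c, so actual power for that outcome could lie above 73%. This stands, and it makes the 73% conditional. It does not repair the paragraph, which applies the 40% to the 92 and takes no credit for record retrieval.

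Two further objections carry less weight. Reading the 40% as a share of those who complete would give 128, but that is not the usual meaning of a dropout rate and the article does not say it. The 92 itself cannot be verified without an SD. The check takes it as the plan's own requirement and asks only whether 128 delivers it.

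A reader might also go further and infer from the dropout allowance that the plan restricts HbA1c to people who stay in the programme, and so discards obtainable data and invites attrition bias between a ten-month and a six-week programme. The documents do not support that. Neither the data collection section nor the section on blood and urine samples limits record extraction to attenders, and the word dropout is left undefined. How non-attenders are followed up is also something an article may leave to the full protocol.

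**Conclusion.** The dropout allowance is wrong as printed. At 40% loss, 128 per group leaves about 77 and not 92, and 154 would be needed. Power for a 0.5% difference is then about 73% rather than 80%, and the difference detectable with 80% power is about 0.55%, above the one the plan calls clinically relevant. The stated 80% holds only up to about 28% loss.

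The shortfall in numbers follows from the printed figures alone. The 73% rests on three conditions: 92 is correct, those who drop out contribute no 16-month outcome, and clustering is ignored. It does not depend on the SD. It should not be read as the power the trial will actually have for HbA1c, since record retrieval may keep the loss below 40%. Equally, the 91% for complete retrieval is a ceiling and not a forecast.

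Record retrieval does not help quality of life, which is collected by interview. The sample size paragraph sizes only HbA1c, so no power figure can be given for that second primary outcome.

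**What to change.** 1. In the sample size paragraph, state that 128 per group gives 80% power only up to about 28% loss and about 73% at 40% loss, and that 154 per group would be needed for 80% power at 40% loss.
2. Because HbA1c is taken from medical records, add that the 16-month value is retrieved for participants who stop attending, where consent allows, so that loss for HbA1c may be below 40%. Say that the 40% still applies to quality of life. It should not be described as sparing the primary outcome in general, because there are two.

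Cost: the first change is wording only and needs no extra patients, but the power stated at 40% loss becomes less favourable. Enrolling 154 instead would add 26 per group, 52 over PTWD and KYS. The second change adds record extraction for non-attenders. Whether the existing consent covers it cannot be checked, because the form is not shown, so this should be confirmed before the sentence is added.

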**Methods/Design:**

We will use a quasi-experimental design with an intervention group (Group 1) and two comparison groups (Groups 2 and 3), N = 128 in each group. Group 1 will receive *Powerful Together with Diabetes*. Group 2 will receive *Know your Sugar*, a six-week group intervention that does not focus on the participants' social environments. Group 3 receives standard care only. Participants in Groups 1 and 2 will be interviewed and physically examined at baseline, 3, 10, and 16 months. We will compare their haemoglobin A1C levels with the haemoglobin A1C levels of Group 3. Main outcome measures are haemoglobin A1C, diabetes-related quality of life, diabetes self-management, health-related, and intermediate outcome measures. We will conduct a process evaluation and a qualitative study to gain more insights into the intervention fidelity, feasibility, and changes in the psychosocial mechanism in the participants' immediate social environments.

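### The enrolment target of 128 per group does not allow for 40% dropout: it leaves about 77 completers per group instead of 92, and about 72 to 73% power instead of 80%

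*Protocol article*

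**What the plan says.** The section on sample size calculation in the protocol article bases the calculation on the decrease in HbA1c at 16 months. It sets the target difference: "A decrease of 0.5% in the intervention group compared to the comparison group will be seen as a difference that is clinically relevant". It gives the number needed for analysis: "at a statistical significance of 5% and a power of 80%, we will need 92 participants in both the intervention and the comparison group". It then allows for losses: "Bearing in mind a dropout rate of 40%, we will need to include 128 people in both the intervention group and the comparison group".

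The same enrolment figure appears in the abstract ("N = 128 in each group") and in the study design section ("The participants who receive the intervention (PTWD, N = 128) will be compared with the participants of the comparison group (KYS, N = 128"). The article gives no standard deviation, no sidedness, no definition of dropout and no formula for the inflation.

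**The concern.** A dropout rate is a fraction of the people enrolled. To end with 92 when 40% leave, the number enrolled must be divided down to 92, so 92 has to be divided by 0.60. The step from 92 to 128 is far too small for that. It looks as if 40% was added to the number of completers.

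This affects the comparison the trial was sized for, PTWD against KYS on HbA1c at 16 months. The discussion makes further implementation depend on whether PTWD lowers HbA1c and improves quality of life. A null result would be read as coming from a trial with a 20% chance of missing a true 0.5% difference. On the plan's own assumptions that chance is more than one in four. The recruitment section itself says that keeping participants from this population in a study is difficult, so high dropout is a realistic planning case.

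**Working it through.** **Inputs, all from the sample size section:** 92 evaluable per group; 80% power; 5% significance; a difference of 0.5%; 40% dropout; 128 enrolled per group.

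**Assumptions, not stated in the article:** a two-sided test (one-sided also checked); equal groups; a comparison of two independent means; and a dropout contributes no 16-month HbA1c.

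**1. Reproducing 128.**
- Multiplying by (1 + dropout): 92 × 1.40 = 128.8. Truncated, this is 128; rounded up, it would be 129.
- Dividing by (1 − dropout): 92/0.60 = 153.3, so 154.

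Only the first form comes close to the printed figure at a 40% rate.

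**2. What 128 delivers at 40% dropout.**
- Completers per group: 128 × 0.60 = 76.8.
- Shortfall: 92 − 76.8 = 15.2, and 15.2/92 = 17%.

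**3. The dropout rate that 128 can bear.** 1 − 92/128 = 28.1%.

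**4. Power with 76.8 per group.** The missing standard deviation is not needed. Stating that 92 per group gives 80% power fixes the ratio of effect to SD.
- At n = 92, the standardised effect is 1.960 + 0.842 = 2.802 (two-sided 5%, normal approximation).
- It scales with the square root of n: 2.802 × √(76.8/92) = 2.802 × 0.9137 = 2.560.
- Power = Φ(2.560 − 1.960) = Φ(0.600) = 72.6%.

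Other versions of the same check:

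| Test | Implied SD | Power, 76 per group | Power, 77 per group |
|---|---|---|---|
| Two-sided, normal | 1.21 | 72.1% | 72.7% |
| Two-sided, t | 1.20 | 72.0% | 72.6% |
| One-sided, normal | 1.36 | 73.1% | 73.6% |
| One-sided, t | 1.36 | 73.0% | 73.5% |

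**5. Type II error.** For the two-sided test it rises from 20% to about 27 to 28%.

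**6. Difference detectable at 80% power.** 0.5 × √(92/76.8) = 0.547, so about 0.55% instead of 0.50%.

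**7. Power by dropout with 128 enrolled (two-sided t).**

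| Dropout | Power at 0.5% |
|---|---|
| 25% | 81.7% |
| 28% | 80.1% |
| 30% | 78.9% |
| 35% | 75.9% |
| 40% | 72.5% |

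**The case against.** The strongest objection is that leaving the programme need not mean losing the outcome. The section on blood and urine samples takes HbA1c at baseline, 10 and 16 months from medical records, where it is measured routinely every three months. Someone who stops attending the groups could still have a 16-month value on file. The planned mixed models can also use participants with incomplete follow-up. The evaluable number could then lie anywhere between about 77 and 128 per group, and power would be at least 80% if outcome loss stayed at or below 28%. This stands as a limit on the power figure: 72 to 73% is conditional on dropouts having no HbA1c. It does not rescue the sentence. The sample size section uses 40% as the loss for which 92 must be inflated, and nowhere says that dropouts still contribute. If a smaller loss was meant, the 40% is the wrong figure.

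Second, the multiplication by 1.40 is inferred. A correct inflation at 28% gives 92/0.72 = 127.8, which rounds up to 128, so a misprinted rate would also fit. The multiplication is the likelier source, but the inconsistency is there on either reading.

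Third, the 92 itself cannot be checked without an SD, and the calculation treats participants as independent although PTWD is delivered in groups of ten. So 72 to 73% is the power relative to the plan's own claim of 80%. It is not an independent estimate of the trial's true power.

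The condensed format of a journal article is no defence here, because the conflict is between printed figures and does not come from an omission.

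**Conclusion.** The concern holds. With 92 needed and 40% dropout, 128 per group is too few: it leaves 76.8, and 154 would be required. On the plan's own pairing of 92 with 80% power, power for a 0.5% difference falls to about 72 to 73% (two-sided) or 73 to 74% (one-sided), and the detectable difference at 80% power rises to about 0.55%.

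That the figures are incompatible rests on arithmetic alone, with dropout read as the share of enrolled participants lost to the analysis. The size of the power loss rests in addition on dropouts having no 16-month HbA1c, and on 92 being right for 80% power. The loss is moderate, but the stated power is wrong as written for the comparison on which the trial was sized.

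**What to change.** Keep 128 per group and correct the dropout sentence in the sample size section. It should say that:

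- with 128 enrolled and 40% dropout, about 77 per group are expected to be evaluable;
- on the assumptions behind the 92, this gives about 72 to 73% power for a 0.5% difference, or 80% power for about 0.55%;
- 80% power for 0.5% holds only if dropout is at most 28%.

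The sentence should also say whether dropout means leaving the programme or having no 16-month HbA1c. If record-based HbA1c is expected for many who leave, the anticipated outcome loss should replace the 40%. The corrected figures should be used when a null result is interpreted. The N = 128 in the abstract and the study design section can stay.

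This costs a short text correction and a less favourable power statement, with no extra participants. The alternative, keeping 80% power at 40% dropout, means 154 per group: 26 more in each, or 308 instead of 256 across PTWD and KYS.

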### Measurements

#### Primary and secondary outcome measures

The primary outcome measures are the HbA1c levels of the participants and diabetes-related quality of life at 16 months after the start of the intervention.

The secondary outcome measures are:

• Diabetes self-management (dietary habits, physical activity, monitoring of blood glucose, medication adherence, smoking, GP visits, body mass index (BMI))

• Health-related outcome measures (blood pressure, heart rate, lipid profile, weight, waist and hip circumference)

Intermediate outcome measures are depression, attitude, knowledge, self-efficacy, coping skills, size and composition of participants' social networks, social support, social influence, social engagement

#### Data collection (procedure of effect evaluation and process evaluation)

Data collection will take place at baseline (T0), after 3 months (T1), after 10 months (T2), and after 16 months (T3) for both the intervention group (PTWD) and the comparison group (KYS). At T1 we will only administer a short structured interview aimed to measure knowledge and DSM. At T0, T2, and T3 we will administer a structured interview and a physical examination. We will study the participants' medical records at all data collection moments. The HbA1c levels of 128 patients who receive standard care will be collected from a large database owned by a GP collective in the Netherlands. See Figure 1 for an overview of the measurements in this study.

**Figure 1 F1:**
[figure not shown]
**Measurements in the DISC Study**.

#### Structured interview

Data on diabetes-related behaviour and psychosocial and intermediate outcome measures will be collected during a structured interview, which will be conducted by a trained interviewer. The questionnaire used in these interviews will be translated and back-translated into Turkish by two qualified independent translators and discussed with the researchers. Rather than Arabic, we expect the majority of our Moroccan participants to speak Berber or Moroccan Arabic. Both are spoken languages only. Therefore, the questionnaire will be translated into Berber and Moroccan Arabic during brainstorming sessions with three native speakers and the researchers in which they will reach consensus about the translation. The questionnaire will be written down phonetically'. The female Moroccan and Turkish respondents and the interviewers will be matched according to gender. The interview will take place in the mother tongue of the participant.

As the target population has a low educational level, we searched for questionnaires that fit this level. Hence, we made a selection of existing questionnaires based on their reliability, validity, and inter-rater reliability among diverse ethnic populations and people in lower SE groups. We pretested the Diabetes Problem-Solving Inventory (DPSI), the Diabetes Social Support Questionnaire DSSQ-Friends Version and DSSQ-Family Version, the Theory of Planned Behaviour (TpB) Questionnaire, and the compilation of the Social Capital Question Bank (see Table 2), and adjusted them to optimally match our respondents' ability to answer the questions. We removed items that our target population did not identify with (face validity) or that were irrelevant for this study. Furthermore, a professional adjusted the literacy level of the questionnaires to the lower educational level of our target population, and we adapted some items to make them more culturally sensitive for the different cultural groups in our study population. For example, in the DPSI we adjusted some of the vignettes to make them more appropriate for our different cultural groups. See Table 2 for an overview of the questionnaires we used.

**Table 2 T2:** Overview of the questionnaires used in the DISC Study

Outcome measure	Questionnaire
Diabetes-related quality of life	Diabetes-specific quality-of-life scale [40]

Depression	4DKL (Four-Dimensional Compliant Questionnaire)

Knowledge	SKILLD (spoken knowledge in low literacy in diabetes scale) [41]

Outcome expectations	OEDM-P (Outcome Expectations for Diabetes Self-Management-positive) OEDM-N (Outcome Expectations for Diabetes Self-Management-negative) [42]

Self-efficacy	Diabetes self-efficacy scale [43,44]

Coping skills	DPSI [45]

Social network	Compilation from the Social Capital Question Bank [46,47]

Social support	DSSQ-Family Version DSSQ-Friends Version [48,49]

Social influence	TpB Questionnaire [50]

